#### Patient reported outcomes

For Dutch burn care, a patient relevant value based healthcare burn core set was developed and implemented in usual care (Spronk et al, submitted). Patient reported outcomes of this value based healthcare burn core set are evaluated in the Burn centres Outcomes Registry the Netherlands (BORN) questionnaires, which are assessed at discharge (including retrospective questions), 2 weeks, 3 months, and 12 months after discharge, and annually afterwards. For all three participating burn centres, the questionnaires are implemented as usual care. The BORN questionnaires include the following topics:

Scar quality of a scar chosen by the patient by POSAS 3.0 patient scale [30];Pain measured by the EuroQol 5D-5L (EQ-5D-5L) [31] pain item and the Patient-Reported Outcomes Measurement Information System (PROMIS) [32] short forms (SF) pain 1a;Self-care measured by the EQ-5D-5L self-care item;Depressive complaints assessed by the EQ-5D-5L item anxiety/depression and PROMIS SF depression 4a;Quality of life measured by the PROMIS Global01 and Global02;Post-traumatic stress symptoms measured by the Impact of Event Scale (IES-6) [33];Independence by a self-developed item independence;Physical functioning assessed by the PROMIS SF physical function 8b;Itching complaints measured by the itch Numeric Rating Scale (itch-NRS) [34];Self-management assessed by the Partners in Health (PIH) scale [35];Return to work or school assessed by the adjusted International Consortium for Health Outcomes Measurement (ICHOM) [36] return to work/school;

#### Patient and treatment characteristics

Demographics, burn characteristics, and treatment characteristics will be obtained from DBR R3.

Demographics: age, gender, medical history, referral, burn centre. Burn characteristics: TBSA, date of burn injury, burn localisation, burn aetiology, inhalation injury. Treatment characteristics: date of initial surgical intervention and thereby time till first surgical intervention (in days), admission on Intensive Care Unit (ICU), ventilation, topical wound treatments, and wound debridement method, type of grafting, other surgical interventions if applicable.

### Data management

Coded research data will be collected and managed in Castor Electronic Data Capture (EDC). Hard copy questionnaires and informed consent files will be maintained within locked cabinets in the burn centre, only accessible to the local research team.

### Sample size

No formal sample size calculation was performed for this prospective study. The sample size was assessed using data from DBR R3 (unpublished data, 2019) and a randomized controlled trial on LDI in patients with indeterminate depth burns in Dutch burn centres [37]. Excluding patients with superficial burns and patients with full-thickness burn injuries, and extrapolating the data to three burn centres, the expected sample size is a maximum of 204 patients for the 18-month study period.

### Statistical analysis

For the statistical analysis descriptive statistics will be used. All parameters will be tested for normality. Depending on the distribution of the data, a mean and standard deviation (normal) or a median and interquartile range (skewed) will be displayed. Differences between the two treatment strategies for the primary outcome measure scar quality and other outcomes will be analysed using two-sided T-test (normally distributed continuous data) or Mann-Whitney U-test (skewed continuous data), and two-sided Chi-square test or Fisher’s exact test (categorical data). Differences between groups in time to event outcomes (i.e. time to surgical intervention and time to wound healing) will be analysed using Kaplan-Meier regression. To correct for the possible influence of patient, burn, and burn centre characteristics on the results, multivariate linear regression (continuous data), multilevel logistic regression (categorical data), and Cox regression (time to event data) will be used. If possible, exploratory analyses will be done on the 10–14 day surgery group. Data analysis will be performed using IBM Statistical Package for the Social Sciences (SPSS) version 26 (SPSS, Chicago, IL, USA) and Python (Python Software Foundation, Delaware, USA).

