## Materials and methods

### Study design

A multicentre prospective study with a 12-month follow-up period will be conducted in the three Dutch burn centres: Maasstad Hospital Rotterdam, Red Cross Hospital Beverwijk, and Martini Hospital Groningen. Patients with deep partial-thickness burns, scanned as yellow by Laser Doppler Imaging (LDI), will be monitored during 18 months; two nine-month periods with either therapy as the treatment of choice in one of the periods. This time period was chosen based on expected numbers and project logistics, such as staffing. Standard care in the Netherlands for deep partial-thickness burns is predominantly conservative treatment with delayed excision and grafting if needed. However, early excision and grafting is applied if deemed more appropriate for a specific patient. The first nine-month period (July 15^th^ 2022 to April 14^th^ 2023) this strategy is followed. In the following nine-month period (April 15^th^ 2023 to January 14^th^ 2024) clinical practice will be changed: early excision and grafting will be the primary treatment. However, in specific cases e.g. based on clinical expertise, conservative treatment can be applied. Depending on the received treatment, patients will be categorized as either the conservative treatment group with delayed excision and grafting if needed, or the early excision and grafting group.

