### Participants

#### Selection

Neither, randomisation nor blinding will take place. The used treatment strategy determines to which group the patient is assigned. The first group represents conservative treatment with delayed excision and grafting if needed, the second group represents early excision and grafting. If a patient is eligible for the study, a member of the research team will provide information about the study. The patient is asked for consent to take additional measurements 12 months after discharge. After reflection time and written informed consent, the patient is included.

Anyone using the protocol must consider the ethical implications of the timing of surgery in their own practice setting. To ensure patient safety, the attending physician is justified in deciding not to start or discontinue treatment from the allocated treatment, based on sound medical grounds and after consulting with the health care team. Deviation from the assigned treatment should be rare, and the reason must be thoroughly documented.

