#### Criteria

Adult (≥18 years) patients with acute thermal burns who are admitted for at least 24 hours or scheduled for surgery are eligible for this study, when the criteria listed below are met.

Inclusion criteria:

Burns with a size of >2.5 centimetres diameter;LDI scan indicating:
Deep partial-thickness burn: yellow wound area on LDI with healing potential between 14 and 21 days, or;Mixed superficial and deep partial-thickness burn: mixed red and yellow wound area on LDI, with a demarcated predominantly yellow area of at least 25cm^2^, or;Mixed full-thickness and deep partial-thickness burn: mixed blue and yellow wound area on LDI, with a demarcated predominantly yellow area of at least 25cm^2^.

The colour codes representing the perfusion units (PU) and healing potential are as follows [8, 23]:

Red/pink: PU 441–2500, healing potential within 14 days;Yellow/green: PU 201–440, healing potential about 14 to 21 days;Blue: PU 0–200, healing potential more than 21 days.

Exclusion criteria:

Frostbite injury [24];Burns suitable for primary closure;Patients unable to complete the Patient and Observer Scar Assessment Scale (POSAS) due to language restrictions or legal incompetence.

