## Discussion

In this protocol we described the aim and specific design attributes of our study to address the gaps in understanding regarding the timing of surgical intervention after deep partial-thickness burn injury. In particular, we intend to compare long-term scar quality, clinical outcomes, and patient-reported outcomes evident after conservative treatment with delayed excision and grafting if needed, and early excision and grafting of deep partial-thickness burns in Dutch burn care. While patient-reported outcomes on this topic are scarce, this study focuses on long-term patient-reported outcomes that will be measured using the POSAS 3.0 and the BORN [38]. POSAS is a unique scar quality assessment tool, as it not only includes the professional’s perspective but also incorporates the patient’s view [39]. BORN provides a wide range of outcomes that were considered important by patients, healthcare professionals, and researchers (Spronk et al, submitted). This will provide insight into the outcomes related to timing of surgical intervention to enable healthcare providers to offer patients more in-depth information when surgery is discussed. The study findings are aimed to support shared decision making in person-centred burn care.

A strength of this study is the multicentre design which improves generalizability and applicability to similarly resourced burn care facilities. Additionally, the homogeneity of the included study burn wound areas is another strength of the study. The followed burns are all deep partial-thickness burns with a comparable healing potential.

A possible limitation might be the absence of donor site quality as an outcome. However, it was deliberately chosen not to include this, since ample literature regarding this topic is available and a recent study on long-term patient-reported scar quality of donor sites was conducted in one of the participating burn centres [13].

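### In a non-randomised study, the primary POSAS comparison is assigned to a normality-gated unadjusted test, with no statement that the planned adjusted regression governs and no LDI depth among the listed burn characteristics

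*Protocol article*

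**What the plan says.** **Allocation.** The Selection section says: "Neither, randomisation nor blinding will take place". The Study design section defines the groups by what was done: "Depending on the received treatment, patients will be categorized as either the conservative treatment group" or the early excision group. In the first period, "early excision and grafting is applied if deemed more appropriate for a specific patient"; in the second, conservative treatment may be given on clinical judgement.

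**Analysis.** The Statistical analysis section says "All parameters will be tested for normality", and then: "Differences between the two treatment strategies for the primary outcome measure scar quality and other outcomes will be analysed using two-sided T-test", with Mann-Whitney as the alternative for skewed data. A later sentence in the same section adds multivariate linear regression for continuous data, to correct for patient, burn and burn centre characteristics. It names no individual covariates and does not rank the two analyses.

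**Depth.** The Patient and treatment characteristics section lists: "Burn characteristics: TBSA, date of burn injury, burn localisation, burn aetiology, inhalation injury". No LDI class, perfusion value or study-wound area appears. The Criteria section admits pure yellow burns, mixed red and yellow burns, and "mixed blue and yellow wound area on LDI, with a demarcated predominantly yellow area" of at least 25 cm². The Discussion nevertheless states: "The followed burns are all deep partial-thickness burns with a comparable healing potential".

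**The concern.** When clinicians choose the treatment and groups follow treatment received, a crude difference in 12-month scar score mixes the effect of treatment with the reasons for choosing it. The plan ties the primary outcome by name to such a crude test and leaves the adjusted model's standing open. If the two disagree, either could be presented as the main result.

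The Introduction's own reasoning marks depth as a likely confounder. Depth and TBSA determine severity, severity is a primary indicator for surgery, and longer healing goes with greater scar risk. TBSA is on the list of characteristics; depth is not.

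The normality test is a lesser point. If it selects Mann-Whitney, the crude result becomes a rank comparison while the regression still estimates a mean difference, so the two no longer address the same quantity. What is at stake is a false or masked treatment effect in results meant to feed a decision aid.

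**Working it through.** The plan gives no power, effect size or SD, so there is no figure of its own to reproduce on this point. Its only sample-size figure is a feasibility maximum of 204 patients (Sample size section). The calculations below show how sensitive the crude test is to confounding; they do not estimate the bias.

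**1. Detectable difference.** Assume 204 patients split 1:1 (102 per group) with none lost by 12 months.
- Standard error in SD units = √(1/102 + 1/102) = 0.140.
- Detectable with 80% power at two-sided 5% = (1.960 + 0.842) × 0.140 = 0.39 SD.
- With a 2:1 split (136 and 68): standard error 0.1485, detectable difference 0.42 SD.

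**2. Possible crude bias.** Bias = imbalance in the share of deeper burns × their outcome difference. All inputs here are assumptions.
- 40% against 20% deeper burns, scarring 0.5 SD worse: 0.20 × 0.5 = 0.10 SD.
- A 30-point imbalance, 0.8 SD worse: 0.30 × 0.8 = 0.24 SD.

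**3. Effect on the crude test when treatment has no effect.** Rejection rate = Φ(b/SE − 1.96) + Φ(−b/SE − 1.96), where b is the bias in SD.

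| Bias b (SD) | 1:1 split | 2:1 split |
|---|---|---|
| 0 | 5% | 5% |
| 0.10 | 11% | 10% |
| 0.20 | 30% | 27% |
| 0.24 | 40% | 37% |
| 0.30 | 57% | 52% |
| 0.40 | 82% | 77% |

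For example, at b = 0.24 and 1:1, b/SE = 1.714 and Φ(−0.246) + Φ(−3.674) = 0.403.

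**4. Does adjustment help without depth?** Simulation with 204 patients, 2,000 runs per scenario and no true effect. Depth is a standard normal variable that influences treatment choice (logit coefficient per SD) and correlates with a normally distributed POSAS score. The regressions also contain one covariate unrelated to treatment or outcome.

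| Logit coefficient | Depth–POSAS correlation | Gated crude test | Regression without depth | Regression with depth |
|---|---|---|---|---|
| 0 | 0.3 | 0.045 | 0.044 | 0.047 |
| 0.5 | 0.2 | 0.088 | 0.090 | 0.036 |
| 0.5 | 0.3 | 0.161 | 0.161 | 0.055 |
| 1.0 | 0.3 | 0.426 | 0.424 | 0.060 |
| 1.0 | 0.4 | 0.655 | 0.657 | 0.054 |

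Under these assumptions, regression without depth does no better than the crude test. Including depth brings the error rate back to about 5%. Covariates correlated with depth would recover part of the gap.

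**5. How much can depth vary?** The eligible band itself covers 201 to 440 perfusion units and healing at about 14 to 21 days. Mixed burns need a demarcated, predominantly yellow area, which narrows the range without closing it. The Introduction says healing potential in these burns varies, whereas the Discussion calls it comparable.

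**6. How readily does the normality test switch?** Shapiro-Wilk at 5% on gamma data, 3,000 runs. At n = 100 it rejects in 6% of samples at skewness 0.1, 10% at 0.2, 18% at 0.3 and 81% at 0.8. At n = 204 it rejects in 16% at skewness 0.2.

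**The case against.** Several stronger readings are tempting, and the article does not support them.

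- **That the primary outcome is analysed only by a crude test.** It is not. The same section plans a linear regression that covers POSAS, and it never calls the crude test the governing result. What stands is that the crude test is the one named for the primary outcome and no ranking is given.
- **That the adjustment omits depth.** This cannot be shown. The list of burn characteristics describes what is drawn from the registry; it is not a declared adjustment set. LDI is an eligibility measurement, depth is naturally a burn characteristic, and a fuller plan that is not shown may include it. Nor does the article support calling depth the strongest confounder, since it names depth together with TBSA. What stands is that depth matters on the article's own reasoning and is not among the characteristics listed.
- **That study wounds span healing from under 14 to over 21 days.** That is the colour range of whole mixed burns. Entry requires a demarcated, predominantly yellow area, and the Observer Scale is scored on the study area. On that reading the Discussion's statement is too strong but not a flat contradiction of the criteria.
- **That the normality test rejects for trivial skew.** At these sample sizes it mostly does not. The gate also acts only on the crude comparison; the regression is not stated to depend on it. The remaining objection is modest: a pretest should not decide what is being estimated.

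Finally, every bias figure is assumed, and the 0.39 SD benchmark uses the maximum sample, equally split and fully followed up.

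**Conclusion.** The concern holds in limited form. Treatment is chosen, groups follow treatment received, and the test attached by name to the primary outcome is unadjusted. Because the planned regression is not designated as primary, a confounded crude result may carry the conclusion. That is a choice the article itself fixes badly, not a detail left to a fuller plan.

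The point on LDI depth is a recommended addition to the model; it is not proof that depth is excluded. The normality gate is secondary.

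The magnitude is unknown. The illustrative 0.10 to 0.24 SD is about a quarter to three fifths of the 0.39 SD detectable difference (0.10/0.39 = 0.26; 0.24/0.39 = 0.62). It depends wholly on assumed imbalances and scar differences, and it describes the crude test, not an adjusted analysis that includes depth. If depth is unrelated to treatment choice, it causes no such inflation. The change is worth making because it is cheap and relies on measurements the study already takes.

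**What to change.** - Name the covariate-adjusted linear model as the primary analysis of POSAS, reported as an adjusted mean difference with a 95% confidence interval.
- Use a mixed model or standard errors clustered by patient, since up to two burns per patient are followed.
- Prespecify the covariates: centre, age, TBSA, localisation, aetiology, LDI class of the study wound (yellow, red and yellow, blue and yellow) or its mean perfusion units, and its area.
- Report the t-test or Mann-Whitney results descriptively. Do not let a normality test choose the estimand; if residuals are skewed, use robust or bootstrap standard errors.
- Qualify the Discussion's statement on comparable healing potential so that it reflects the width of the yellow band and the admission of mixed burns.

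**Cost:** revised analysis wording, a few degrees of freedom, and extraction of LDI class or perfusion and wound area from scans already made for eligibility. No new measurement of patients is needed. Adjustment reduces bias from measured characteristics only; unmeasured reasons for choosing a treatment remain a limitation to state.

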### Primary outcome

#### Scar quality

The primary outcome measure of the study is long-term scar quality assessed with the POSAS (generic version, 3.0) 12 months after discharge. The POSAS is a widely used scar quality measurement instrument that comprises two separate scales: the Patient Scale and the Observer Scale [30]. The Patient Scale includes 17 questions about visual, tactile and sensory characteristics, and the overall opinion. The Observer Scale includes eight questions assessing the scar’s pigmentation, vascularity, surface level, surface texture, firmness, adherence, tension, and overall opinion. Each item is rated on a five-point scale. The lowest score is ‘1’, which corresponds to the situation of normal skin (i.e. normal pigmentation, no itching). Score ‘5’ equals the largest difference from normal skin (i.e. the worst imaginable scar or sensation) [30].

The Patient Scale is assessed by the patient, and two independent observers assess the Observer Scale on the study area(s). The assessment is mostly done during the standard 12-month outpatient appointment by the attending burn physician(s) and/or by members of the research team. If there is no standard 12-month outpatient appointment planned, the patient is invited to attend the clinic for the scar quality assessment, for which travel and parking expenses are reimbursed. All members of the research team and the burn physicians are trained to assess scar quality with the POSAS. Each burn centre’s highly experienced head of research provides a POSAS training on the latest version: POSAS 3.0 [30].

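### The repeated continuous BORN scales (secondary outcomes) are assigned single-visit tests and single-level regression, with no main time point, so earlier scores go unused

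*Protocol article*

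**What the plan says.** Under Patient reported outcomes, the article describes the BORN questionnaires, "which are assessed at discharge (including retrospective questions), 2 weeks, 3 months, and 12 months after discharge, and annually afterwards". The Study design section sets the horizon: "A multicentre prospective study with a 12-month follow-up period will be conducted in the three Dutch burn centres". Four BORN assessments therefore fall within the study's follow-up, and the yearly forms come after it.

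The Statistical analysis section covers these scales under its general rule: "Differences between the two treatment strategies for the primary outcome measure scar quality and other outcomes will be analysed using two-sided T-test" if normally distributed, a Mann-Whitney test if skewed, and chi-square or Fisher tests for categorical items. The adjusted analyses are introduced with "To correct for the possible influence of patient, burn, and burn centre characteristics on the results", and the methods are "multivariate linear regression (continuous data), multilevel logistic regression (categorical data), and Cox regression (time to event data) will be used". The word multilevel is attached to the logistic model alone, and the level is not identified. No BORN visit is named as the main one.

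The primary outcome is different: "long-term scar quality assessed with the POSAS (generic version, 3.0) 12 months after discharge". That is a single time point, and this point does not touch it.

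**The concern.** The methods named for continuous outcomes take one value per patient, whereas the BORN scales supply up to four within a year. The section does more than leave the choice open: it names methods for all outcomes other than the primary, and the ones named for continuous data have no place for repeated measurements. The same sentence gives categorical data a multilevel model and continuous data none, without a reason.

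Two consequences follow. First, a comparison at 12 months drops every patient without a 12-month form, although that patient's scores at discharge, 2 weeks and 3 months may be on file. Second, with no main visit named, each scale can yield four group comparisons, and the reader cannot tell which one is the result. Patient-reported outcomes are part of the stated aim and are meant to inform the decision aid, so it matters which number is carried forward.

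**Working it through.** There is no planned figure to reproduce. The Sample size section gives a maximum of 204 patients from a feasibility extrapolation, without a formal calculation. The article states no significance level, correlation, dropout rate or group split.

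**Inputs**
- From the article: 204 patients at most; four BORN visits within 12 months.
- Assumed: equal split (204 / 2 = 102 per group); two-sided 5% level; equal correlation rho between any two visits of one patient, at 0.3, 0.5 and 0.7; no true difference unless stated.

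**1. Is a t-test at one visit valid?** Each patient contributes one value, so correlation between visits does not enter. In simulation (4,000 runs per rho) the false-positive rate at each visit was 4.4% to 5.4% for every rho. The test is valid.

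**2. Four visit tests per scale.** If the visits were independent, the chance of at least one false positive would be 1 − 0.95^4 = 18.5%. Correlation lowers it:

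| rho | 8,000 runs | 4,000 runs |
|---|---|---|
| 0.3 | 16.8% | 16.5% |
| 0.5 | 15.8% | 15.1% |
| 0.7 | 13.0% | 13.1% |

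The range is 13% to 17% per scale.

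**3. Missing 12-month forms.** Let the probability of missing the 12-month form depend on the 3-month score, with no true 12-month difference, and compare observed cases only.
- *Dependence in one group only*, logit P(missing) = −1.0 + 0.8 × score against −1.0 (27% to 29% missing): bias 0.06, 0.10 and 0.15 SD at a 3-to-12-month correlation of 0.3, 0.5 and 0.7.
- *Other forms of unequal dependence*, logit P(missing) = −0.85 + s × score, correlation 0.6:

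| s in the two groups | Bias (SD) | False-positive rate |
|---|---|---|
| 0.5 and 0 | 0.09 | 8% |
| 1 and 0 | 0.17 | 17% |
| 0.5 and −0.5 | 0.18 | 19% |

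- *Same dependence in both groups* (29% to 34% missing): bias 0.00 to 0.02 SD in absolute size, even when the groups differ by 0.3 SD at 3 months.
- *Likelihood estimate using the 3-month score*, in the settings with correlation 0.6: bias below 0.001 SD.

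For scale, the standard error of a two-group difference with complete data is sqrt(2/102) = 0.140 SD. A bias of 0.06 to 0.18 SD is therefore about 0.4 to 1.3 standard errors (0.06 / 0.140 and 0.18 / 0.140).

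**4. What a mixed model adds.** With complete data and an unstructured covariance, its 12-month contrast is essentially the ordinary 12-month comparison. The gain lies in patients whose 12-month form is missing and in having one named result.

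**The case against.** The best defence is that this is a condensed article. The reporting time point, the handling of missing data and multiplicity for secondary outcomes are commonly settled in a statistical analysis plan, which is not shown. That stands for pure silence. It does not cover the method choice: the section names methods for these outcomes, and those for continuous data do not use the repeated measurements.

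Four stronger readings are tempting, and the article supports none of them.

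- *The tests ignore within-patient correlation and are therefore invalid.* That would be so only if visits were pooled as independent rows, and nothing in the article says they are.
- *The comparison is biased by dropout.* The article gives no dropout rate or mechanism. Bias arises only when missingness depends on earlier scores differently by group.
- *Pre-burn differences bias the comparison and the planned adjustment misses them.* Confounding is a fair worry, since "Neither, randomisation nor blinding will take place. The used treatment strategy determines to which group the patient is assigned". But the article says only that the discharge form includes retrospective questions; that these concern the pre-burn state is an assumption. Adjustment for patient characteristics is planned, and the variables collected ("Demographics: age, gender, medical history, referral, burn centre") include medical history. A repeated-measures model would not remove confounding by itself.
- *Categorical items have the same gap.* A multilevel logistic model is named, and its level may already be the patient.

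The 13% to 17% also deserves a caveat: it matters only if a significant result at any one visit would be read as a finding, which the article neither says nor rules out.

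**Conclusion.** The point holds for the continuous BORN scales, as secondary outcomes. The named methods are valid at a single visit but leave collected data unused, and no main time point is fixed. The cost is a 13% to 17% chance of at least one false positive per scale if all four visits are tested. There is also a possible bias of about 0.06 to 0.18 SD at 12 months if dropout depends on earlier scores differently by group, and almost none if the dependence is the same. These sizes rest on an assumed equal split of 204 patients, a two-sided 5% level, correlations of 0.3 to 0.7 and roughly 30% missing at 12 months. None of these except the 204 comes from the article. The change is worth making because it is cheap and standard, not because the planned comparison has been shown to be wrong.

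**What to change.** In the Statistical analysis section:

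1. For each repeated continuous BORN scale, specify one linear mixed model with group, visit as a categorical term, group-by-visit, the patient, burn and centre covariates already planned, and a within-patient covariance. Use all available visits. Treat discharge as an outcome visit and not as a baseline, because early surgery will usually have taken place by then.
2. Name the 12-month group contrast as the single main comparison for each scale; present the other visits as descriptive.
3. State that the multilevel logistic model for categorical BORN items has patient as a level.
4. If the retrospective discharge questions cover the pre-burn state, add that score as a covariate in a sensitivity analysis only. It is recalled after treatment and may be coloured by recovery.

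The cost is a few sentences and slightly more programming, with no new data, visits or patients; the software named in the article can fit these models. The mixed model relies on a missing-at-random assumption, which should be stated.
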